# 3.1 Site Assessment

### 3.1.0 Objectives

1. Establish the background knowledge of mid-level health practitioners in malaria, tuberculosis and HIV/AIDS
2. Establish the range of tasks performed by mid-level health practitioners with regard to management of malaria, tuberculosis and HIV/AIDS
3. Assess the quality of recording of data in the various registers used by the health centre
4. Document available facilities that support On-Site Training
5. Identify health facilities that have two clinical officers
6. Identify health facilities that have a functional laboratory that can perform basic tests

### 3.1.1 Methods

Primarily quantitative techniques of data collection were employed in this assessment. This was complimented with key informant interviews and document review. Data was collected from all cadres of health professionals present at the facility including some who were off-duty for the day. A total of five different tools were administered at every visited site. Facility Checklist (observation):

- HMIS data quality guide
- Learning needs assessment guide
- Laboratory personnel assessment guide
- Facility laboratory assessment guide
- Facility in-charge key informant guide

The key documents reviewed include the staff list, HMIS105 & 108 report forms, comprehensive HIV including ART monthly reports from every facility visited as well as all registers in use at the facilities.

Prior to the assessment, the questionnaires were pre-tested in three Kampala City Council (KCC) clinics in Kampala. The pre-test was among others used to assess consistency, accuracy and feasibility of the questionnaires and before the main assessment was conducted. The pre-test also helped gather information on comprehension of the questions.

Five teams of graduate researchers consisting of one Laboratory Technician and two Social Scientists administered the tools at the selected sites. The teams underwent a rigorous one-day training sessions focusing on the objectives of the assessment, assessment design and data collection.

Structured questionnaires and key informant interview guides served as the primary tools for data collection. Information regarding data/records was obtained from the registers with the help of the persons that manage them most of the time. Data on the completeness of the records rather than the patient information were recorded. Data on clinic performance and standards of care were obtained from HMIS 105&108 report forms.

### 3.1.2 Design

This assessment adopted a descriptive design employing quantitative methods of data collection as well as key informant interviews with the in-charge at the site. Structured questionnaires and key informant interview guides served as the primary tools for data collection. Review of facility reports and registers was also done.

### 3.1.3 Setting

A total of 45 purposively selected health facilities (sites) were visited across the country. The sites were drawn from all the six major regions of the country i.e. West Nile, Northern Uganda, Eastern Uganda, Central, Western, and South Western Uganda. The sites visited were a mix of Hospitals, Health Center (HC) IVs and HC IIIs.

The sites for assessment were purposively selected following a well laid out criteria. A listing of all health facilities meeting the criteria was obtained from MoH’s Quality of Care Initiative. The list was developed following the outlined criteria below:

- The health facility had to be a HC IV or comparable facility such as a small general hospital, large HC III or non-governmental organization clinic
- It had to be an active ART site or accredited ART site that is scheduled to become active by April 2009
- No past or current participation in MoH quality improvement programs such as Health Care Improvement (HCI) Project or HIVQual
- No past or current participation in a partnership with the U.S. Department of Defense
- Has a population of potential patients who are not prisoners
- Representation from all six administrative regions of Uganda

Reconnaissance calls to confirm the operational status of the health facility were made to the potential sites prior to the assessment. All the 45 sites visited met the inclusion criteria outlined above.

### 3.1.4 Population

At every site visited attempts were made to adopt total coverage of all the health professionals available on site. Participants in the assessment included doctors, clinical officers, nurses, midwives, nursing assistants and laboratory personnel, among others. An inventory of staff for the various sites was obtained from the District Health Office (DHO), verified on-site by the head of the facility, and was used to calculate the response rate for the learning needs assessment for clinical and laboratory staff. Those who did not participate were either on study leave, off-duty or out of station.

At the selected sites, the first contact was the in-charge of the health centre / hospital or his/her designees. This person served as the key informant who provided general information about the site including the number of available clinical officers. The head of the laboratory was in turn asked to help with the assessment for the functionality of the laboratory.

### 3.1.5 Ethical considerations

**Background**

The site assessment was completed before IDCAP was reviewed by the Makerere University Faculty of Medicine Research Ethics Committee (SOMREC) and Uganda National Committee on Science and Technology (UNCST). The assessment collected descriptive data to guide curriculum development and site selection. The principal investigators did not consider it research, because no hypotheses were tested. At the request of SOMREC, this component of the evaluation is included in the proposal.

**Consent**

The evaluators sought informed consent from the participants as a best practice for any endeavor that involves collecting data from human beings. Verbal informed consent was requested from each participant. In the case of the Learning Needs Assessment and Key Informant Interview, there was a formal process in which participants were informed that the interviews were voluntary and confidential. “Confidential” means the participants names were not be linked the data that are entered into the database and only aggregate results were presented.

**Data storage**

No human names were recorded on any of the questionnaires and facility name was only recorded on the Key Informant Interview Guide. All sites were identified by a site number on all questionnaires except the Key Informant Guide; it would not be possible to identify individual participants from those paper forms. The key linking the site number to the facility name was kept securely.

Participants were informed that the data were confidential rather than anonymous, because a determined person who had access to the key might be able to identify an individual respondent if s/he was the only person who reported a specific profession at a health facility.

### 3.1.6 Limitations

Training needs as measured by previous training and self-assessment of competence. A review of studies of health professionals in the United States and Europe concluded that the validity of self-assessment of performance was low to moderate. Consequently, the assessment provides only a gross estimate of training needs. More detailed information based on observation of practice by the clinical mentors and more innovative method such as trainee diaries, in which health professionals note difficult situations during patient encounters.[[18]](#endnote-19)

Also, the health professionals were a convenience sample of those who were at the sample of accredited ART clinics on the day of the assessment. Consequently the sample over represented some types of professionals at some facilities and under-represented others; doctors were underrepresented at all facilities.

# 3.2 Competence and practice of MLP

### 3.2.1 Methods

The first specific objective is to “evaluate the effectiveness of the integrated Infectious Disease Training in preparing mid-level practitioners to perform key clinical tasks corresponding to infectious disease competencies at acceptable standard.” Two mid-level practitioners from each of 36 sites will be invited to a Core Infectious Diseases course at IDI. The unit of analysis will be the individual. The evaluation design will be a before/after comparison of trainee skills and performance.

Individual trainees will complete eight to 12 written case scenarios and be observed in clinical practice at three times during the core course: Pretest, post 3-week session, post 9-month classroom and distance program.

IDI routinely evaluates the knowledge of its trainees with multiple choice tests and clinical practice with observation of trainees at the Adult Infectious Diseases Clinic. Trainees must obtain a passing score on these activities to be awarded a certificate. Trainee scores are confidential. Trainees can retake the knowledge test and observation of clinical practice until they pass. These evaluations are similar to any educational program that grants diplomas or degrees on the basis of assessment of student/trainee accomplishments and are generally exempt from ethical review.

The IDCAP evaluation is the same as the routine IDI evaluation in the sense that trainees must obtain a passing score to be awarded a certificate and trainee scores will be confidential. It differs from the routine IDI evaluation in the methods of assessment: 1) the knowledge test will require answers to open-ended questions rather than multiple choice questions, and 2) observation of clinical skills will occur at the trainee’s health facility rather than at the Adult Infectious Diseases Clinic.

### 3.2.2 Design

The alternative hypothesis that IDT has a significant effect on trainee competence and practice will be tested with a before/after comparison. The indicators of infectious disease competencies at baseline will be compared to those measures at the end of each session of the IDT core and booster courses. The indicators will be used to establish an acceptable standard, and we will test for differences in the percentage of MLP who meet the standard between baseline and subsequent measures. In regression analysis, we will adjust for unobserved differences across MLP using a random effects model and the *xtgee* command in Stata version 10. We will also compare change in competence between Arms A and B to test the incremental impact of OSS

on the proportion of MLP who meet the standards.

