# ABSTRACT

This evaluation aim is to investigate a cost-effective way to build capacity for the care and prevention of infectious diseases among mid-level practitioners in sub-Saharan Africa. Classroom based training continues to be the dominant form of training, despite evidence that suggests that on-site support (OSS) is more beneficial. Definitive evidence that on-site support is the most effective way to deliver the required outputs and related outcomes is still lacking. IDCAP will provide two interventions that integrate training in TB, HIV/AIDS and malaria as well as other infectious diseases, and the effects will be studied.

**Infectious Disease Training (IDT)** - An integrated core curriculum for MLP in the comprehensive care and prevention of infectious disease, delivered to 72 MLP from 36 health facilities at IDI in three sessions for a total of five weeks with extensive clinical sessions.

**On-Site Support Services (OSS)** – CQI activities and a set of responsive Multidisciplinary Clinical Training (MCT) modules for use at the clinic level with teams of medical officers, clinical officers, nurses and midwives, laboratory technicians and records keepers will be sequentially delivered to the 36 facilities in two phases. Sites will be randomly assigned to either Phase 1 or 2.

The evaluation of the capacity-building program will assess the impact of IDT on individual performance and impact of OSS on cost, clinic performance and health outcomes, and definitively test whether or not the incremental impact of on-site support services relative to classroom training alone can be cost-effective. The four alternative hypotheses are:

1. An Integrated IDT course for mid-level practitioners is effective at building the skills required to perform key clinical tasks at acceptable standards
2. Onsite Multidisciplinary Team training and Continuous Quality Improvement activities (or On-Site Support- OSS) significantly improve clinic performance
3. OSS activities are cost effective
4. After monthly OSS for nine months during Phase 1 at Phase 1 sites, bi-monthly OSS for six months has an additional effect on facility performance

For hypothesis 1, the unit of analysis will be the individual trainee. The effect of IDT on capacity and practice will be measured with a pre/post comparison and by comparing the performance of the trainees at the end of the training program to an objective standard.

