# CHAPTER THREE: METHODOLOGY

## 3.0 Overview

##

There are four major components of the evaluation design as described below: 1) Site Assessment, 2) Competence and practice of individual MLP who participate in IDT, 3) Facility cost and performance indicators, and 4) Mortality survey. The site assessment guided the curriculum development and site selection. As shown in Figure 1, it occurred only once in Year 1. The competence and practice of individual MLP will be evaluated with methods that are currently used by the Infectious Diseases Institute (IDI) to evaluate trainees. Data on MLP will be collected three times: a) before training, b) after the three-week course, and c) after the nine-month program that includes two, one-week booster courses and distance learning. Facility performance indicators will be collected on a monthly basis from each site. Data for external quality assurance of laboratory performance will be collected at baseline and end of the intervention or analyzed as secondary monthly data from the Tuberculosis National Reference Laboratory. Sites will be randomly assigned to begin OSS in either Phase 1 or Phase 2 and the facility indicators of these two samples of sites will be compared. The principal investigators of IDCAP are actively considering collecting data on mortality among children under five, but a final decision has not been made. At the request of the acting chairperson of SOMREC, we are including information about this potential activity. Mortality surveys would be conducted before and after the OSS. In this chapter, each component of the evaluation is described separately.

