### 3.2.4 Population

Participants will be MLP who enroll in the Core IDT. Calculations of the number of participants required were based on the average scores of the pretest (42%) and post test (62%) for the Comprehensive HIV Care Including ART course during 12 separate occasions when it was taught at IDI. The standard deviation of scores for all participants was .11. The standard deviation of scores within groups at each occasion when the course was taught was .12 and the correlation between before and after test scores within a group was 0.5.

There are two approaches to considering sample size here, both of which are simplified versions of the analysis. The first is a single sample of individuals, who are tested before and after the three-week Core IDT. Participants from phase 1 and phase 2 sites are not expected to differ, because OSS has not started at the Phase 1 sites. A sample size of 13 would be needed to detect a change in average test score from .4 (pretest) to .5 (post test).

The second is a comparison of two groups: participants from phase 1 site and participants from phase 2 sites. At the end of the nine-month after IDT, participants from the phase 1 sites will have also benefited from OSS and their scores would increase more than participants from phase 2 sites. Each group has an average before test score (either pretest or after the three-week Core IDT) and an average nine-month test score and hence an average of differences in scores between before and nine-months. The effect will be the difference in average differences between the groups. A sample size of 23 participants in each group would be needed to detect a difference in change in scores of .1.

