### 3.2.6 Limitations

The success of the proposed intervention will depend on our ability to integrate it within other existing training activities, to avoid duplication of the considerable efforts to date. The diversity of training providers in Uganda is substantial, and coordination of those efforts must happen from within the Ugandan government. IDI is well positioned to facilitate this effort for IDT, as it has effectively worked with the MOH to have the Joint Uganda Malaria Training Program approved by the National Malaria Control Program and the National Malaria Case Management Technical Working Group. Many organizations have made major contributions to the body of training materials and learning approaches, and we intend to work closely with those partners to ensure our collective success. Most importantly, the WHO has established training materials that all parties view as essential and complementary, and working to ensure that this program builds on that foundation will be a high priority.

Another possible limitation would be attrition of the health professionals who have been trained. In collaboration with the Ministry of Health (MOH), IDCAP has built-in mechanisms to increase retention in the evaluation sites and institutionalize the quality improvements.

1. The district health officers have been asked to refrain from transferring the trainees in the core Infectious Disease Training (IDT) for 12 months and preferably 24 months after attending the IDT.
2. IDT trainees may be motivated to stay at the IDCAP sites until they complete the nine-month IDT, because they will benefit from distance learning and booster sessions at IDI as well as receiving an IDI certificate. In addition, the MOH’s Director of Clinical Services has encouraged IDI to make the IDT a degree program at Makerere University. Although creating a degree program will take longer than nine months, there is a precedent for awarding a degree retroactively. Participants in Hospice Uganda’s nine-month, palliative care course were awarded a degree retroactively when the course became a degree program.
3. Based on the SOMREC’s comments, IDI has decided to offer a fifth session of the IDT mid-way through phase 1. At sites where the IDT trainees have transferred or otherwise left, a replacement will be identified to attend this additional session.

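### Booster and nine-month tests of the classroom course (IDT) set no restriction by phase, so as written they credit about half of the on-site support (OSS) effect to IDT

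*Protocol*

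**What the plan says.** Specific objective 1 and hypothesis 1 concern the effect of IDT on mid-level practitioners. Section 3.2.2 sets the test: "The indicators of infectious disease competencies at baseline will be compared to those measures at the end of each session of the IDT core and" (the boosters are named next). It adds that "we will test for differences in the percentage of MLP who meet the standard between baseline and subsequent measures". The Abstract adds a second criterion, "by comparing the performance of the trainees at the end of the training program to an objective standard". Section 3.0 places the last of three measurements "after the nine-month program that includes two, one-week booster courses and distance learning".

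Section 3.2.4 describes OSS exposure at two of these times. At the three-week test, "Participants from phase 1 and phase 2 sites are not expected to differ, because OSS has not started at the Phase 1 sites". Later, "At the end of the nine-month after IDT, participants from the phase 1 sites will have also benefited from OSS and their scores would increase" by more than those of Phase 2-site participants.

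Section 3.2.2 also plans to compare the change in competence between Arms A and B (taken here as Phase 1 and Phase 2 sites). It describes that comparison as a test of OSS. Section 3.2.6 adds that "IDI has decided to offer a fifth session of the IDT mid-way through phase 1", for replacements at sites where trainees have left.

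**The concern.** The three-week measure is free of OSS. The nine-month measure is not, and neither is any booster measure that falls after OSS has started. Half of the sites are in Phase 1, so about half of the trainees carry a second intervention that the protocol itself expects to raise their scores. No text for the hypothesis 1 test limits it to Phase 2-site trainees or includes a phase term. The random-effects adjustment in section 3.2.2 deals with unobserved differences between practitioners, not with OSS exposure. The comparison of arms estimates OSS but does not take it out of the before/after change or out of the percentage meeting the standard.

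The evaluation sets out to separate classroom training from on-site support. A late IDT result that contains OSS could be cited as evidence that the classroom course alone brings practitioners to standard.

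**Working it through.** **Inputs.** Sections 2.3 and 3.2.4 give 36 sites, 18 per phase, two trainees per site and 72 in total, so 36 per phase. Section 3.2.4 gives a within-group SD of 0.12, an overall SD of 0.11, a before/after correlation of 0.5, a detectable change of 0.10 for each calculation, and stated sizes of 13 (single sample) and 23 per group (difference in change). Two-sided alpha of 0.05 and 80% power are assumed here. Section 3.3.4 gives alpha of 0.05 and 80% power for the site-level calculation, but 3.2.4 gives neither.

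**The protocol's own figures.** SD of change = 0.12 × √(2 × (1 − 0.5)) = 0.12.

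- Single sample: n = (1.96 + 0.842)² × 0.12² / 0.10² = 11.3, so 12 by the normal formula and 14 by the paired t. The stated 13 lies between. An SD of 0.11 with 90% power gives 12.7, so 13.
- Two groups: n = 2 × (1.96 + 0.842)² × 0.12² / 0.10² = 22.6, so 23 per group, as stated.

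The sample sizes are not in question.

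**What the unrestricted late comparison estimates.** Mean change over all 72 = IDT effect + (36/72) × OSS effect.

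| Assumed OSS effect | Overstatement of IDT | Share of the 0.10 sizing change | Share of the 0.20 past gain (42% to 62%) |
|---|---|---|---|
| 0.05 | 0.025 | 25% | 12.5% |
| 0.10 | 0.05 | 50% | 25% |

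**Effect on the test.** As a limiting case, suppose IDT had no effect and OSS added 0.10. The standard error over 72 is 0.12/√72 = 0.0141, so z = 0.05/0.0141 = 3.54. The chance of a significant before/after result is then about 0.94. It falls to 0.90 if the spread between arms enters the standard error. With an assumed correlation of 0.2 to 0.5 between the two trainees at a site, it is 0.78 to 0.90. If OSS adds 0.05, the chance is about 0.30 to 0.42.

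**What is left if only Phase 2-site trainees are used.** For a 0.10 change with n = 36, the standard error is 0.12/√36 = 0.02 and z = 5, so power is 0.999. With an assumed within-site correlation of 0.5, power is 0.98. For a change of only 0.05, power is 0.71, or 0.53 with that correlation.

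The distortion in the percentage meeting the standard cannot be sized, because the protocol gives no numerical standard.

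**The case against.** **Pooling is inferred.** The protocol never says that the nine-month estimate ignores phase. Section 3.2.4 calls its calculations simplified versions of the analysis. It ties the single sample to the three-week test and treats the phases as two groups at nine months. The authors plainly saw the difference in exposure, and section 3.2.2 may be incomplete rather than a decision to pool. Regression terms are often left to an analysis plan. This stands in part. Even so, the written test of hypothesis 1 covers the booster measures with no restriction, and the Abstract applies the standard to the trainees as a whole.

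**The needed estimate is nearly produced already.** The comparison of arms contains the Phase 2 group's own mean change. That is true, so the data can answer hypothesis 1 at nine months. But no text names that change as the IDT estimate.

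**The size depends on assumptions.** The 0.10 OSS effect is a detectable difference, not a forecast. Against past gains of about 0.20, an overstatement of 0.05 would be unlikely to alter the direction or significance of the result. This stands, and it is why a range is given.

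**Replacement trainees.** A reader might infer that replacements from Phase 2 sites will have had OSS by their final test. That assumes they follow a full nine-month schedule and enter this analysis. The protocol states neither, nor how many replacements there will be.

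**Conclusion.** The point holds for measures taken after OSS has started. As written, the late before/after change is the IDT effect plus about half of the OSS effect. That is an overstatement of 0.025 to 0.05 if OSS adds an assumed 0.05 to 0.10, with equal numbers per phase. The percentage meeting the standard is affected in the same direction, by an unknown amount.

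A reader might infer that hypothesis 1 goes unanswered. The documents do not support this: the three-week comparison is free of OSS, can use all 72 trainees and needs 13. Nor do they support the inference that the OSS results are compromised. The effect of OSS on facility performance rests on the randomised comparison of phases, and the cost-effectiveness analyses use facility indicators or mortality rather than the trainees' before/after change. The high rejection probabilities above describe a limiting case with no IDT effect, which past course results give no reason to expect.

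**What to change.** In section 3.2.2, with matching wording in the Abstract:

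- Use all 72 trainees for the IDT effect at the three-week measure.
- For any measure taken after OSS has started, take the IDT change and the percentage meeting the standard from Phase 2-site trainees who have not yet received OSS. Equivalently, use the control-arm time effect from a model with an arm-by-time term.
- Report Phase 1-site trainees at those measures as IDT plus OSS.
- If replacement trainees from the added session are analysed, apply the same rule to any score taken after OSS starts at their site.
- State that the Phase 2-site estimate is an uncontrolled before/after change. It may include secular trend and the effect of the concurrent programmes acknowledged in section 3.3.6, and restricting by phase does not remove these.

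The change is to analysis wording only, with no new data. Its price is about 36 trainees instead of 72 for the late IDT estimate. That is ample for a 0.10 change but less so for a change near 0.05.

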## 2.3 Research Question

Two sets of questions will be addressed.

1) Is an Integrated ID Training course (classroom and distance learning) for mid-level practitioners effective at building the skills required to perform key clinical tasks at acceptable standards? To answer this question, 2 mid-level practitioners from each of 36 sites will be invited to a Core Infectious Diseases course at IDI. The unit of analysis will be the individual. The evaluation design will be a before/after comparison of trainee skills and performance.

2) Does Onsite Multidisciplinary Team training and Continuous Quality Improvement activities, which is called On-Site Support (OSS), significantly improve clinic performance and health outcomes? If yes, are the OSS activities cost-effective? To answer these questions, 36 sites will receive the OSS activities for nine months, but 18 will be randomly assigned to receive the OSS in phase 1 and the others will receive it nine months later. The unit of analysis will be the site, and the evaluation design is a randomized trial of sites on key performance indicators.

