### Based on IDI’s experience with the Joint Uganda Malaria Training Program (JUMP), the Core IDT was designed for two participants from each site. As explained in Section 3.3.4 with the sample size calculations for the facility cost and performance indicators, a sample size of 18 sites per treatment group or total of 36 sites was required. Consequently 72 participants would attend the Core IDT course. The evaluation is adequately powered to assess changes in case scenario scores, particularly as we have observed changes of double the magnitude that were used in the sample size calculations.

###

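### Section 3.2 compares trainees from Phase 1 and Phase 2 sites to test OSS, which is randomised by site, without accounting for site

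*Protocol*

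**What the plan says.** OSS is allocated to sites. The Abstract states: "Sites will be randomly assigned to either Phase 1 or 2". Section 2.3 gives the split: "18 will be randomly assigned to receive the OSS in phase 1 and the others will receive it nine months later". Section 3.2.1 brings in the trainees: "Two mid-level practitioners from each of 36 sites will be invited to a Core Infectious Diseases course at IDI". The same section makes the individual the unit of analysis for this component.

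Section 3.2.2 first describes a before/after test of the training course. For the regression it states "we will adjust for unobserved differences across MLP using a random effects model" and names Stata's xtgee. It then adds a comparison of Arms A and B (read here as Phase 1 and Phase 2 sites) to test the increment from OSS "on the proportion of MLP who meet the standards". No model is attached to that second comparison.

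Section 3.2.4 sizes the Phase 1 versus Phase 2 comparison on a different scale, the mean change in test score: "A sample size of 23 participants in each group would be needed to detect a difference in change in scores of .1". The text that closes the section notes "Consequently 72 participants would attend the Core IDT course" and concludes "The evaluation is adequately powered to assess changes in case scenario scores".

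Section 3.2 contains no site term, no clustering by site and no within-site correlation.

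**The concern.** The A versus B contrast estimates the effect of something assigned to 36 sites, not to 72 people. Two trainees at one site work alongside the same OSS-supported team, and their clinical practice is observed at that facility, so their outcomes may be correlated. A trainee-level effect handles repeated measures on one person. It does nothing for the correlation between the two colleagues. If that correlation is positive and ignored, the standard error of the OSS effect is too small and the test rejects too often.

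There is a second, smaller gap. The sample size and the statement of adequate power concern mean scores, while the outcome named for the OSS contrast is a pass proportion. A reader could carry the power statement over to the proportion, for which no calculation is given.

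**Working it through.** **Inputs from the protocol.** 36 sites, 18 per arm, two trainees each, so 36 trainees per arm (2.3, 3.2.1). Score SD .12 within groups, before/after correlation .5, difference to detect .1 (3.2.4). Section 3.2.4 states neither power nor alpha; 80% and .05 are taken from Section 3.3.4, and a two-sided test is assumed.

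**Inputs assumed.** The within-site correlation (ICC) and the pass mark are not given, so ranges are shown.

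1. *The plan's own figure.* SD of change = .12 × √(2 × (1 − .5)) = .12. Per group, 2 × (.12/.1)² × 7.849 = 22.6, rounded up to 23. This matches the protocol and treats trainees as independent.

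2. *Sample size with site clustering.* The design effect for two per site is 1 + (2 − 1) × ICC = 1 + ICC. Needed per arm: 22.6 × 1.1 = 24.9, so 25 (ICC .1); 22.6 × 1.2 = 27.1, so 28 (.2); 22.6 × 1.5 = 33.9, so 34 (.5). The 36 available suffice up to an ICC of about 36/22.6 − 1 = .59.

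3. *Power for mean scores at 36 per arm.* The effective number is 36/(1 + ICC), i.e. 36, 30 and 24 for ICC 0, .2 and .5. With d = .1/.12 = .833 and a noncentral t distribution, power is about 94%, 89% and 81%. With 36 site-level values on 34 degrees of freedom it is about 93%, 88% and 80%.

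4. *Type I error if site is ignored, for scores.* This is 2 × [1 − Φ(1.96/√(1 + ICC))].
   - ICC .1: 6.2%
   - ICC .2: 1.96/1.095 = 1.789, giving 7.4%
   - ICC .5: 1.96/1.225 = 1.600, giving 11.0%

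5. *The same for a pass proportion near 50%.* If the ICC is a correlation between normal scores, cutting at the median reduces it to (2/π) × arcsin(ICC): .2 becomes .128 and .5 becomes .333. Type I error is then 6.5% (1.96/√1.128 = 1.845) and 9.0% (1.96/√1.333 = 1.697).

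6. *Power for the pass proportion at nine months.* With normal scores, SD .12 and the same .1 shift, the Phase 1 pass rate is Φ(Φ⁻¹(p) + .833), where p is the Phase 2 pass rate. Pooled two-proportion formula, no clustering:

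| Phase 2 pass rate | Phase 1 pass rate | Power, 36 per arm | Needed per arm |
|---|---|---|---|
| 10% | 33% | 66% | 50 |
| 30% | 62% | 79% | 37 |
| 50% | 80% | 77% | 40 |
| 70% | 91% | 63% | 53 |
| 80% | 95% | 51% | 72 |

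The maximum over all pass marks is 79.6%. Clustering lowers the 50% row to about 68% if an ICC of .2 applies to the pass indicator itself (effective number 30), or about 71% if .2 applies to the scores (36/1.128 = 31.9).

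**The case against.** The strongest reply is that the random-effects sentence belongs to the before/after test of the course. The A versus B comparison comes afterwards with no model named, and the panel variable and variance estimator could be left to an analysis plan that is not shown. That is fair as far as it goes. But the section fixes the individual as its unit, the only dependence it mentions is across trainees, and its sample size assumes independence. An analysis plan that followed this text would leave site out.

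Three stronger readings are tempting and should be resisted.

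- A reader might infer that the claim of adequate power is false. It is not. It is made for case scenario scores, and steps 2 and 3 bear it out under moderate clustering. No power is claimed for the pass proportion, and Section 3.2.4 itself describes its calculations as simplified.
- A reader might infer that the proportion is the wrong outcome because it discards information. Meeting an objective standard is the protocol's own question (2.3, 2.4, hypothesis 1b), so replacing it is a trade-off and not a correction.
- A reader might infer that the trial's main test of OSS is affected. That test (hypothesis 2, Section 3.3.2) is a regression of clinic-level data, at the level of randomisation. The trainee contrast is ancillary to it.

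Two further objections limit the size. Case scenarios are completed at IDI and not at the site, so shared site conditions bear mainly on observed practice. Stable site differences also largely cancel in change scores. Both suggest that the relevant correlation may be low, but neither makes it zero. The proportion figures compare nine-month pass rates, not changes in them, and the rows with high pass rates rest on nothing in the protocol.

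**Conclusion.** The point stands for the Phase 1 versus Phase 2 comparison of trainees. OSS is assigned by site, nothing in Section 3.2 accounts for site, and the 23 per group assumes independent trainees. For an assumed ICC of .2 to .5, a nominal 5% test has a true level of about 7% to 11% for scores. For a pass proportion near 50% it is about 6.5% to 9%, if the correlation is at score level. At an ICC of .1 the score-level figure is only 6.2%.

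The design is large enough for mean scores, with about 89% power at an ICC of .2 and 81% at .5. For the pass proportion the protocol makes no power statement. Under normal scores with SD .12, the same shift gives just under 80% power at best before clustering, and clearly less where most trainees pass. All these sizes rest on an assumed ICC, and the proportion results also on an assumed pass mark. The before/after test of the course and the site-level OSS analysis are outside this point.

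**What to change.** For the OSS contrast in Section 3.2.2, name the site as the cluster. Any of three routes will do: xtgee with the site as panel and a small-sample correction for 36 clusters; a model with a site random effect; or an analysis of 36 site-level values. Say which is meant, because xtgee fits a population-averaged model and not a random effects model.

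In Section 3.2.4, restate the requirement as about 22.6 × (1 + ICC) per arm with the assumed ICC given, and state that the adequacy claim is for mean scores only. The proportion meeting the standard may remain the tested outcome. Give its power for a stated pass mark, and report the clustered mean-score comparison alongside it.

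The cost is wording in the protocol and the analysis plan, with no extra data. Relative to an analysis that ignores site, score intervals widen by about √1.2 = 1.10 at an ICC of .2 and √1.5 = 1.22 at .5. That is the width the design supports.
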